### 4.3. Endpoints

#### Primary Endpoints

The nature, frequency, and severity of adverse events (AEs) and/or serious adverse events (SAEs) associated with administration of BPSC1001 at 5 different doses measured as follow:

- Frequency and severity of local injection site reactogenicity signs and symptoms: pain, erythema, and induration until day 14 post vaccination (solicited local symptoms)
- Frequency and severity of systemic reactogenicity signs and symptoms until day 14 post vaccination (solicited general symptoms)
- Frequency of adverse events (AEs), severity and assessed relationship to study products until day 28 post vaccination (unsolicited AE)
- Detailed description of all serious adverse events (SAEs) until day 28 post vaccination
- Distribution of values of safety laboratory measures at baseline and at follow-up visits post-vaccination until day 28 post vaccination (reference ranges will be age appropriate)
- Number of participants with early discontinuation of vaccinations and reason for discontinuation until day 28 post vaccination

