## **Solicited Adverse Events**

A solicited AE is a predetermined event, which may reflect safety concerns related to the investigational product. The solicited AEs for this study include:

- Swelling, or pain at site of injection
- Fever
- Chills
- Myalgia (described to the subject as generalized muscle aches)
- Arthralgia (described to the subject as generalized joint aches)
- Swelling of joint(s) or pain on motion of joint(s)
- Rash or blisters of the skin
- Blisters or ulcers in mouth, tongue or gums
- Fatigue
- Headache
- Gastrointestinal symptoms (nausea, vomiting, abdominal pain, and/or diarrhea)

Participants with objective signs of arthritis (swelling, tenderness, warmth etc) will be evaluated with ultrasound.

Vesicular lesions and joint effusions (if tapped) will be sampled for PCR and virus isolation.

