### Severity Assessment

All AEs will be assessed for severity by the investigator. Inherent in this assessment is the medical and clinical consideration of all information surrounding the event including any medical intervention required. Each event will be assigned one of the following categories: mild, moderate, severe, or life-threatening. Refer to the grading scale in annex 2 for further guidance in the assignment of severity. The criteria below may be used for any symptom not included in the grading scale. Any grade 4 (life-threatening) AE must be reported as an SAE.

The CRF for AEs will reflect only the highest severity for continuous days an event occurred.

- Mild      Grade 1      Does not interfere with routine activities  
Minimal level of discomfort
- Moderate      Grade 2      Interferes with routine activities  
Moderate level of discomfort
- Severe      Grade 3      Unable to perform routine activities  
Significant level of discomfort
- Potentially life-threatening      Grade 4      Hospitalization or ER visit for  
potentially  
life-threatening event

FDA guidelines for toxicity will be followed; however, if a subject is evaluated in an emergency room for nonlife threatening illness or symptoms (ie, visits emergency department on weekend for mild problems because the physician's office is closed), the information from that visit will be reviewed and severity of the adverse event will be assessed according to the subject's clinical signs and symptoms.

As defined by the ICH guideline for GCP, the term "severe" is often used to describe intensity (severity) of a specific event (as in mild, moderate, or severe myocardial infarction); the event itself however, may be of relatively minor medical significance (such as severe headache). This is not the same as "serious", which is based on subject/event outcome or action criteria usually associated with events that pose a threat to a subject's life or functioning. Seriousness (not severity) serves as a guide for defining regulatory reporting obligations.

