### **Adverse events**

An AE is any untoward medical occurrence in a subject that may occur during or after administration of an Investigational Medicinal Product (IMP) and does not necessarily have a causal relationship with the intervention. An AE can therefore be any unfavorable and unintended sign (including an abnormal laboratory finding), symptom or disease temporally associated with the study intervention, whether or not considered related to the study intervention.

Each AE will be graded according to the tables for AE severity below. The following guidelines will be used to determine whether or not an AE is recorded in the study database:

- Solicited AE (*i.e.*, reactogenicity parameters) will be recorded on diary cards in the seven days and recorded in the CRF in the 14 days following injection
- Unsolicited AE of all severities will be recorded on diary cards in the seven days and recorded in the CRF in the 28 days following injection
- After Day 28 and throughout the remainder of the study period, only SAE will be recorded in the CRF

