| Toxicity grading scale for systemic adverse events |                               |                                 |                                      |                                             |
|----------------------------------------------------|-------------------------------|---------------------------------|--------------------------------------|---------------------------------------------|
| Systemic sign/symptom                              | Grade 1

Mild           | Grade 2

Moderate         | Grade 3

Severe                | Grade 4

Potentially life-threatening |
| Headache                                           | No interference with activity | Some interference with activity | Significant; prevents daily activity | Medical consultation and/or hospitalization |
| Fatigue                                            | No interference with activity | Some interference with activity | Significant; prevents daily activity | Medical consultation or hospitalization     |
| Myalgia                                            | No interference with activity | Some interference with activity | Significant; prevents daily activity | Medical consultation and/or hospitalization |
| Arthralgia                                         | No interference with activity | Some interference with activity | Significant; prevents daily activity | Medical consultation and/or hospitalization |
| Chills                                             | No interference with activity | Some interference with activity | Significant; prevents daily activity | Medical consultation and/or hospitalization |
| Sweats                                             | No interference with activity | Some interference with activity | Significant; prevents daily activity | Medical consultation and/or hospitalization |

|                         |                               |                                                                    |                                                           |                                             |
|-------------------------|-------------------------------|--------------------------------------------------------------------|-----------------------------------------------------------|---------------------------------------------|

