| Subjective Fever        | No interference with activity | Some interference with activity                                    | Significant; prevents daily activity                      | Medical consultation and/or hospitalization |
| Nausea                  | No interference with activity | Some interference with activity not requiring medical intervention | Prevents daily activity and requires medical intervention | Medical consultation and/or hospitalization |
| Vomiting                | No interference with activity | Some interference with activity not requiring medical intervention | Prevents daily activity and requires medical intervention | Medical consultation and/or hospitalization |
| Abdominal Pain          | No interference with activity | Some interference with activity not requiring medical intervention | Prevents daily activity and requires medical intervention | Medical consultation and/or hospitalization |
| Diarrhea                | No interference with activity | Some interference with activity not requiring medical intervention | Prevents daily activity and requires medical intervention | Medical consultation and/or hospitalization |
| Other systemic symptoms | No interference with activity | Some interference with activity                                    | Prevents daily activity                                   | Medical consultation and/or hospitalization |

From the FDA's 2007 voluntary guidance:

(<http://www.fda.gov/downloads/BiologicsBloodVaccines/GuidanceComplianceRegulatoryInformation/Guidances/Vaccines/ucm091977.pdf>)

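### The four gastrointestinal rows of the annex severity scale leave two combinations without a Grade 1–3 cell, so the same event can be graded 2 or 3 and Grade 3 is not comparable across symptoms

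*Protocol*

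**What the plan says.** The annex, under Assessment of severity, gives a toxicity scale for systemic adverse events. In the nausea, vomiting, abdominal pain and diarrhoea rows the wording is identical. Grade 1 is no interference with activity, Grade 2 is "Some interference with activity not requiring medical intervention", Grade 3 is "Prevents daily activity and requires medical intervention" and Grade 4 is "Medical consultation and/or hospitalization".

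The headache, fatigue, myalgia, arthralgia, chills, sweats and subjective fever rows define Grade 3 as "Significant; prevents daily activity". The row for other systemic symptoms also uses activity only.

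Three statements govern how the scale is used:

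- The annex, under Adverse events, says: "Each AE will be graded according to the tables for AE severity below".
- Section 6.5, Severity Assessment, leaves severity to the investigator, requires every event to be placed in one of four categories, and describes the annex scale as guidance.
- Section 6.5 then lists general criteria, in which Grade 3 is inability to carry out routine activities with significant discomfort. It limits their scope: "The criteria below may be used for any symptom not included in the grading scale".

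Section 6.5 lists the four gastrointestinal symptoms among the solicited adverse events. Section 4.3 makes the frequency and severity of solicited general symptoms to day 14 a primary endpoint.

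**The concern.** Grades 2 and 3 in the four gastrointestinal rows each join two conditions: one on activity and one on whether medical intervention is required. The conditions are paired so that only the matching combinations are covered. A volunteer whose vomiting stops all daily activity but does not require intervention fails Grade 3 on the second condition. The same volunteer exceeds Grade 2 on the first. A volunteer with an equally disabling headache is Grade 3 without further question.

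The general criteria do not formally close the gap, because they are offered only for symptoms that the scale omits, and these four are in it. The rater therefore has to assign a category, finds no cell that fits, and reads in one place that the tables are applied and in another that they are guidance.

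The protocol's analysis of safety is mainly descriptive (section 7), so the table of grades by dose group is itself the primary result on severity. If Grade 3 has one definition for headache and a narrower, incomplete one for vomiting, the columns of that table cannot be read across symptoms. A statistical analysis plan cannot repair this afterwards if raters resolved the same event differently at source.

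**Working it through.** No figure in the protocol is in dispute, so the check is an enumeration of the wording.

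**Inputs.** Activity limitation has three levels in the scale: none, some, prevents. Intervention required has two: no, yes. That gives 3 × 2 = 6 combinations. Grade 4 turns on a different criterion (consultation or hospitalisation) and is set aside here, then taken up below.

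| Activity | Intervention required | Four gastrointestinal rows, as written | Other systemic rows | Gastrointestinal rows graded on activity only |
|---|---|---|---|---|
| None | No | Grade 1 | Grade 1 | Grade 1 |
| None | Yes | Grade 1 | Grade 1 | Grade 1 |
| Some | No | Grade 2 | Grade 2 | Grade 2 |
| Some | Yes | no cell | Grade 2 | Grade 2 |
| Prevents | No | no cell | Grade 3 | Grade 3 |
| Prevents | Yes | Grade 3 | Grade 3 | Grade 3 |

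**Result.** As written, 4 of 6 combinations have a grade and 2 of 6 do not, in each of the four gastrointestinal rows. The other eight systemic rows have no gap. Activity-only anchors leave the four defined combinations where they are and fill only the two empty ones.

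**Grade 4.** An event with some interference that requires intervention may meet Grade 4 if a consultation takes place, so that combination is not always without a grade. The same overlap touches the defined Grade 3 cell: an event that requires intervention will often involve a consultation.

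**Effect on the endpoint.** Section 6.5 demands a category for every event, and the annex records solicited events in the case report form without regard to grade. The frequency component is therefore unchanged. For an event that prevents activity without requiring intervention, the category is undetermined: Grade 3 if the rater gives weight to activity, Grade 2 if the unmet intervention condition decides.

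**Size per event.** The number of such events is not in the protocol. What follows from the planned cohort sizes in the synopsis is the weight of one participant whose grade turns on this choice. That is 1/20 = 5.0 percentage points in a cohort of 20, 1/39 = 2.6 in cohort 2 and 1/62 = 1.6 in cohort 3.

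**The case against.** The strongest reply is that the investigator's judgement covers the gap. Section 6.5 asks for all information around an event to be weighed, calls the scale guidance and requires one of four categories. A sensible investigator would put a volunteer disabled by vomiting in Grade 3. That may happen, but nothing in the text directs it, and the annex sentence about applying the tables points the other way. This reply does defeat one tempting inference: that such events go ungraded or fall out of the primary severity count. Nothing in the protocol excludes or leaves uncounted an event that fits no cell.

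A reader might also equate the gap with symptoms that were untreated or managed at home. The scale says that intervention is required, which is a clinical judgement. A volunteer may require intervention without having received it. An estimate built on the share of untreated symptoms would measure something else, and every input to it would be an assumption, so no participant count is offered.

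On impact, the holding rules in section 4.6 turn on related serious events, on suspected unexpected serious reactions that are life-threatening or fatal, and on the investigator's opinion. They do not use Grade 3 counts. Fisher's test in section 7 compares the proportion reporting adverse events, which the grade does not change. Both points stand and limit the matter to the severity summary. The overlap with Grade 4 can also push grades upward, so a net understatement of overall severity is not shown. What can be said is that gastrointestinal Grade 3 may be understated.

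Finally, the annex attributes the scale to an FDA guidance document that is not at hand, so whether the wording is inherited could not be checked. The consortium also wants data that can be combined across sites. Neither point removes the gap. Because the proposed change moves no combination that already has a grade, the harmonisation objection has little force, though partner sites should know of it.

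**Conclusion.** The defect is in the text and does not depend on any numerical assumption: two of six combinations in the four gastrointestinal rows have no Grade 1–3 cell, and the general criteria do not formally apply to these symptoms. The consequence is inconsistent assignment between Grades 2 and 3, and a Grade 3 for gastrointestinal symptoms that cannot be compared with Grade 3 for the other systemic symptoms in a primary severity endpoint. Followed literally, the scale denies Grade 3 to a disabling gastrointestinal reaction that requires no intervention, which is more than a missing detail.

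The conclusion goes no further than that. Events are not lost, frequencies are unaffected, and how many participants are concerned cannot be derived from the protocol. It should be corrected, and correction is cheap.

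**What to change.** Reconcile three places so that each combination maps to one grade: section 6.5 Severity Assessment, the Adverse events part of the annex, and the systemic grading scale.

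- In the four gastrointestinal rows, grade on activity as the other systemic rows do: some interference is Grade 2, and prevention of daily activity is Grade 3. Drop the intervention clauses from both cells.
- Record whether medical intervention was required as a separate case report form field, so that the information is kept.
- State once whether the annex tables bind the rater or guide the rater.
- Apply the mapping to all cohorts. Section 4.1 gives 60 participants already vaccinated in cohorts 1 to 3 (20 + 39 + 1 = 60). Their gastrointestinal grades should be re-derived where the recorded data allow. The protocol does not show whether activity level was captured separately from the grade.

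The cost is a wording change in four table rows, one data field and a note to raters. The downside is possibly a few more Grade 3 events. Partner sites using the same scale should be told of the mapping so that pooled severity tables use one rule.
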